### Statistical analysis

Data will be presented as medians with quartile range. The Mann–Whitney U test will be used for comparisons of median values between groups. The calculations will be performed with PASW Statistics 18 version 18.0.0, Polar Engineering and Consulting®.

For the categorical data analysis (for the primary end point and selected secondary end points) data will be organized in contingency tables, tested for difference between observed and expected values and appropriate tests will be applied to test the null hypothesis of no difference between the groups (chi-square or Fischer’s exact test) with StatsDirect version 2.7.9 (StatsDirect Ltd., England, UK). The differences will be regarded significant at p<0.05. Statistical methods will be applied for intention-to-treat and per protocol analysis.

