### Sample size

We decided to use decrease of ALT by 0.3 upper limit of normal value as the primary endpoint of the study. It was estimated that a sample size of 80 patients would be sufficient to reveal a difference in the treatment effect of 30% (45% in experimental group vs. 15% in control group) considering α = 0.05 and a power (β) of 80%. The number of 80 children accounted for approximately 20% withdrawals or losses. The sample size was calculated with StatDirect software version 2.7.9 (StatsDirect Ltd., England, UK).

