## Conduct of the trial

### Study visits overview

The study will be divided into the selection period, treatment period and the follow-up.

In the selection period patients were carefully screened to confirm diagnosis of NAFLD and to identify any potential exclusion criteria.

On the first visit at week 0 (M0) patients with NAFLD undergo wide-range physical, anthropometric, laboratory and imaging investigations. When eligible they are included in the study, randomized and receive study drug or placebo. At the same time patients are consulted by dietician, report 3-day food record, FFQ and IPAQ. They are instructed about their individual low-calorie diet and how to keep increased level of physical activity.

During the treatment period next two visits are planned:

M1 at 12 weeks after the inclusion,

M2 at 24 weeks after the inclusion.

At visit M1 a routine physical examination along with simplified laboratory tests and anthropometry are done. Patients report their complaints and adverse events to the physician and consult their diet with a dietician.

At visit M2 patients undergo physical examination, comprehensive laboratory and imaging examinations. Repeated food and physical activity questionnaires are recorded. Patients stop taking the study drug however the lifestyle recommendations are further maintained.

A follow-up visit (M3) is scheduled 6 months after the end of therapy to check whether changes of body weight, laboratory parameters of liver function and imaging are sustained.

Blood tests measurements perform the local laboratories, except for antioxidants, cytokines and fatty acids profile that are sent to the central laboratory. Upper limit of normal of ALT activity varies between the four medical centers (40–45 U/L), therefore in the statistical analysis we will calculate and use a percentage of the ULN.

Each anthropometric parameter and vital sign was measured twice and the mean value was taken into statistics. Systolic/diastolic blood pressure and heart rate were measured by the automatic blood pressure device (Dinamap XL, Critikon®, U.S.). Patients rested for 10 minutes in the supine position before measurement. Arm circumference was set midway between the shoulder tip and the olecranon process. The same arm was used throughout the study.

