### Randomization

Eligible participants who fulfilled inclusion criteria were randomized into the trial. Using computer statistical software StatsDirect version 2.7.9 (StatsDirect Ltd., England, UK) the list of random treatment assignments was generated. Randomization was made to two arms (omega-3 or placebo), in blocks of four individuals, stratified by centre. The use of centre stratification guarantees balance and increases statistical accuracy. Investigators sent randomizations requests by fax to the central randomization center (CRC) responsible for the process of randomization. In return they received a random number that was subsequently allocated to the choice of one of the products (numbered 100 or 101).

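### The primary responder comparison ignores the centre strata used in randomisation and leaves chi-square or Fisher open; one centre-stratified test should be named before unblinding

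*Protocol article*

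**What the plan says.** The Statistical analysis section states that, for the primary and selected secondary endpoints, "data will be organized in contingency tables, tested for difference between observed and expected values and appropriate tests will be applied". The tests it then offers are chi-square or Fisher's exact test. It mentions no stratification, covariate, expected-count threshold or continuity correction. The significance rule is "The differences will be regarded significant at p<0.05", with sidedness not given.

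The Randomization section describes allocation in blocks of four, stratified by centre, and gives the reason: "The use of centre stratification guarantees balance and increases statistical accuracy".

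The endpoint is a responder count: "We decided to use decrease of ALT by 0.3 upper limit of normal value as the primary endpoint of the study". Outcome measures places it after six months of treatment. Inclusion criteria require ALT of at least 1.3 ULN and list no upper limit.

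**The concern.** There are two separate weaknesses.

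- **Design and analysis do not match.** The article stratifies by centre to gain accuracy, but both named tests pool over centre. Balance by centre lowers the true variability of the treatment difference when centres respond differently. A pooled test does not credit this, so its standard error is then too large and the gain is not collected.
- **The primary test is not fixed.** At this sample size Fisher's test is clearly more conservative than uncorrected chi-square. If the choice is made after the data are seen, a borderline result can be called either way.

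A lesser point is baseline ALT. A fixed fall of 0.3 ULN is a different relative demand at different starting values, so response may vary with baseline, and neither test takes baseline into account.

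**Working it through.** **Inputs from the article.** Response 45% vs 15%, alpha 0.05, power 80%, N = 80 including about 20% losses (Sample size); 38 randomised per arm (Results); four centres (Participant selection). Two-sided testing is assumed.

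**1. The plan's own figure.** The unpooled two-proportion formula gives n = (1.960 + 0.842)² × (0.45 × 0.55 + 0.15 × 0.85) / 0.30² = 7.851 × 0.375 / 0.09 = 32.7, so 33 per arm. Then 33 × 1.2 = 39.6, so 40 per arm and 80 in total. The stated 80 is reproduced. With 20% losses, 80 × 0.8 = 64, or 32 per arm.

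**2. Chi-square against Fisher.** Exact power is the sum over all responder counts (a, b) of Bin(a; n, 0.45) × Bin(b; n, 0.15), taken where the test gives p < 0.05. Disagreement is the same sum where only one test is significant.

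| Per arm | Chi-square, uncorrected | Fisher | Verdicts differ |
|---|---|---|---|
| 38 | 84.0% | 77.6% | 6.5% |
| 32 | 77.2% | 68.8% | 8.4% |

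With no treatment effect (common response 15% to 45%) the verdicts differ in about 2 to 3% of trials.

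**3. Example tables at 38 per arm.** For 13 vs 5 responders, X² = 76 × (13 × 33 − 5 × 25)² / (38 × 38 × 18 × 58) = 76 × 304² / 1,507,536 = 4.66, p = 0.031. With the Yates correction, 304 becomes 304 − 38 = 266 and X² = 3.57, p = 0.059.

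| Responders | Chi-square | Yates | Fisher | Smallest expected count |
|---|---|---|---|---|
| 13 vs 5 | 0.031 | 0.059 | 0.057 | 9 |
| 14 vs 6 | 0.037 | 0.068 | 0.067 | 10 |
| 16 vs 8 | 0.048 | 0.084 | 0.083 | 12 |

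**4. Pooled against centre-stratified test.** This needs centre response rates and centre sizes, which the article does not give, so both are assumed. The simulation used four equal centres, blocks of four, 3,000 trials per setting, overall rates 45% vs 15%, and uncorrected tests.

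| Centre SD (logit scale, assumed) | 76 patients: chi-square / CMH power | 64 patients: chi-square / CMH power |
|---|---|---|
| 0 | 84.6% / 84.3% | 77.5% / 76.5% |
| 0.5 | 83.1% / 84.0% | 78.0% / 78.2% |
| 1.0 | 85.3% / 88.5% | 79.2% / 83.0% |

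At SD 1.0 the gain is 3.2 and 3.8 points. The pooled test's type I error there is 3.5% and 3.4%, against 5.1% and 5.0% for CMH. A second simulation (20,000 trials, centre response rates 10% to 50%, 38 per arm) gave 85.7% vs 87.4%, a gain of 1.7 points, with type I error 3.9% vs 5.2%.

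**5. Baseline ALT.** The required relative fall is 0.3 / 1.3 = 23% at the entry limit, 0.3 / 3 = 10% at 3 ULN and 0.3 / 5 = 6% at 5 ULN. This makes dependence on baseline plausible but does not measure it. In one simulation, adjusting for baseline added about 0 to 2 points of power. In another, with assumed logit slopes of 0.5 to 1.0 per SD of baseline, adjusting for centre and baseline added a nominal 3 to 8 points. That figure is overstated, because the adjusted test's type I error was 5.6 to 6.7%.

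**The case against.** The best defence is that the reference to observed and expected values is a loosely worded expected-count rule. If the conventional threshold of 5 is meant, chi-square would be chosen in all three tables above, and at the planned effect with 38 per arm an expected count below 5 almost never arises (under 0.01% of trials). This narrows the point but does not close it. No threshold is printed, and chi-square with the Yates correction gives non-significant results in the same three tables, so the word chi-square alone does not fix the verdict.

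It can also be said that a fuller analysis plan may specify a stratified or adjusted analysis. That is fair for a supporting model. The article does, however, state the primary tests itself, and neither is stratified.

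Some stronger readings are not supported:

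- **That the unstratified test is invalid.** It is not; ignoring centre makes it at worst conservative.
- **That response is known to depend on baseline ALT.** The article nowhere says so. Chance imbalance in baseline is already covered by the error rate of the randomised comparison.
- **That differing laboratory limits undermine the pooled test.** The article notes that "Upper limit of normal of ALT activity varies between the four medical centers (40–45 U/L" and, in the same sentence, plans to analyse ALT relative to each centre's limit.
- **That each centre's radiologist affects the result.** The radiologist scores steatosis, a secondary outcome, and does not measure ALT.
- **That the verdict will probably turn on the test.** At the planned effect the two tests agree in more than 91% of trials at 32 per arm and more than 93% at 38.

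Finally, naming CMH alone would recreate the ambiguity. With responders spread evenly over assumed centres of 10, 10, 9 and 9 per arm, 13 vs 5 gives about p = 0.035 uncorrected and 0.065 corrected. The correction must be stated too.

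**Conclusion.** The point holds in limited form, at low to moderate severity. The named primary tests do not use the randomisation strata, and the choice between them has no clear rule.

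The firmest part is the open choice. Using the plan's own rates and two-sided testing, it moves power by 84.0 − 77.6 = 6.4 points at 38 per arm and 77.2 − 68.8 = 8.4 points at 32. Fisher at 32 per arm falls 11.2 points short of the planned 80%.

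The cost of ignoring centre is smaller and rests on assumption: none if centres respond alike, about 2 to 4 points of power if they differ strongly. The gain from baseline adjustment is expected to be small unless the dependence is strong, which nothing in the article establishes.

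**What to change.** Before unblinding, replace the two-test wording for the primary endpoint with one named analysis: the Cochran-Mantel-Haenszel test stratified by centre, without continuity correction, two-sided at 0.05, at week 24, reported with the stratified risk difference and its 95% CI. Name as a supporting analysis a logistic model with arm, centre and baseline ALT/ULN.

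The cost is a sentence or two in the plan and a few lines of code. Centre and baseline ALT are already recorded, no extra patients are needed, and if centres respond alike the change in power is negligible (84.6% vs 84.3% with 76 patients). The Results section says the 24-week data were still being finalised and the full analysis was yet to come, so at that stage the change could still be made in advance.

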## Conduct of the trial

### Study visits overview

The study will be divided into the selection period, treatment period and the follow-up.

In the selection period patients were carefully screened to confirm diagnosis of NAFLD and to identify any potential exclusion criteria.

On the first visit at week 0 (M0) patients with NAFLD undergo wide-range physical, anthropometric, laboratory and imaging investigations. When eligible they are included in the study, randomized and receive study drug or placebo. At the same time patients are consulted by dietician, report 3-day food record, FFQ and IPAQ. They are instructed about their individual low-calorie diet and how to keep increased level of physical activity.

During the treatment period next two visits are planned:

M1 at 12 weeks after the inclusion,

M2 at 24 weeks after the inclusion.

At visit M1 a routine physical examination along with simplified laboratory tests and anthropometry are done. Patients report their complaints and adverse events to the physician and consult their diet with a dietician.

At visit M2 patients undergo physical examination, comprehensive laboratory and imaging examinations. Repeated food and physical activity questionnaires are recorded. Patients stop taking the study drug however the lifestyle recommendations are further maintained.

A follow-up visit (M3) is scheduled 6 months after the end of therapy to check whether changes of body weight, laboratory parameters of liver function and imaging are sustained.

Blood tests measurements perform the local laboratories, except for antioxidants, cytokines and fatty acids profile that are sent to the central laboratory. Upper limit of normal of ALT activity varies between the four medical centers (40–45 U/L), therefore in the statistical analysis we will calculate and use a percentage of the ULN.

Each anthropometric parameter and vital sign was measured twice and the mean value was taken into statistics. Systolic/diastolic blood pressure and heart rate were measured by the automatic blood pressure device (Dinamap XL, Critikon®, U.S.). Patients rested for 10 minutes in the supine position before measurement. Arm circumference was set midway between the shoulder tip and the olecranon process. The same arm was used throughout the study.

One experienced radiologist was performing abdominal ultrasound at each centre and estimated the degree of liver steatosis according to Saverymuttu scoring system [29]. When applicable, liver biopsy was done and assessed by two independent pathologists. At each centre a registered dietician administered food records and monitored adherence to the dietary regime.

At every visit any adverse events (AEs), that have occurred since the last visit and changes in the concomitant treatment were documented. For all investigations the data were entered into electronic case report form (eCRF) system and stored there anonymously.

The detailed schedule of the trial visits and investigations are summarized in Table 2.

**Table 2 T2:** Investigation schedule

**Procedure**	**Inclusion**	**Treatment period**		**Follow-up**
	**M0**	**M1**	**M2**	**M3**
	**Week 0**	**Week 12**	**Week 24**	**Week 48**
**Written consent**	X			
**Medical history**	X	X	X	X
**Randomization**	X			
**Study drug dispensing**	X	X		
**End of study drug treatment**			X	
**Compliance**		X	X	X
**Adverse events monitoring**		X	X	X
**Previous and concomitant treatment**	X	X	X	X
**Vital signs and physical examination**	X	X	X	X
**Anthropometry + TANITA® bioimpedance**	X	X	X	X
**Abdominal utrasound**	X		X	X
^**a**^**Liver biopsy**	X			
**Dietary assessment:**				
- dietetic counseling	X	X	X	X
- 3 day food record	X			
- FFQ	X		X	
**Physical activity:**				
- general counselling	X	X	X	X
- IPAQ	X		X	
**Laboratory tests:**				
- hematology	X		X	
- ALT,AST, GGTP, bilirubin, INR	X	X	X	X
- fasting glucose, insulin	X	X	X	X
- OGTT glucose, insulin 0-240mins	X			
- fasting lipids profile	X		X	X
- adipokines, cytokines, antioxidants	X		X	
- fatty acid composition of plasma phospholipids	X		X	
^**a**^**DEXA**	X		X	
^**a**^**MRI - body fat distribution**	X		X	
^**a**^**1H-MRS - liver fat content**	X		X	

^a^Done in selected patients.

Vital signs: mean BP, HR and temperature.

Anthropometry includes measurements of body weight and height, waist, hips and mid upper arm circumference (IOTF, WHO), triceps, abdominal and subscapular skin fold thickness.

OGTT glucose and insulin measurements were performed in intervals every 30 minutes from 0 to 240 minutes.

### Randomization

Eligible participants who fulfilled inclusion criteria were randomized into the trial. Using computer statistical software StatsDirect version 2.7.9 (StatsDirect Ltd., England, UK) the list of random treatment assignments was generated. Randomization was made to two arms (omega-3 or placebo), in blocks of four individuals, stratified by centre. The use of centre stratification guarantees balance and increases statistical accuracy. Investigators sent randomizations requests by fax to the central randomization center (CRC) responsible for the process of randomization. In return they received a random number that was subsequently allocated to the choice of one of the products (numbered 100 or 101).

### Treatment dispensing and assessment of compliance

All the study treatments were provided in a capsule form. Identical appearance of capsules for both arms (omega-3 and placebo) ensured the double blind study design. Study drug were stored in plastic boxes containing 200 capsules at room temperature. The boxes were the same for the two treatments arms, blinded by a manufacturer, marked with 3 digits: “100” or “101” – for omega-3 or placebo.

Study treatment was dispensed by the investigator at the inclusion visit M0. After the validation of patient’s eligibility the investigator contacted with the CRC to declare the inclusion of the patient and allocate his/her therapeutic unit number. The kit number attributed by CRC corresponded to the randomized treatment arm. The box marked with respective kit number were given to the patient.

At the visit M1 the treatment pack allocated at the previous visit was retrieved from the patient and the drug accountability of the remaining capsules was performed.

At the final M2 study visit the kits allocated at visits M0 and M1 were retrieved from the patient. The number of used and remaining capsules were documented to estimate the compliance with the study drug. When the study had been completed no new allocation of treatment was made.

## Results

Patients recruitment for the trial started in 2008 and ended in 2011. From a total of 86 screened participants 10 were found ineligible (11.6%). The most frequent reason for ineligibility was ALT activity <1.3x ULN. A total of 76 children with NAFLD met the inclusion criteria and were randomly assigned to receive either the omega-3 (n=38) or placebo (n=38).

The follow-up of the study is still ongoing. We are currently finalizing data collection obtained after 24 weeks of treatment. The full statistical analysis of the study results will be completed in the mid-2013.

## Discussion

Marine omega-3 fatty acids are very promising dietary supplements used in prevention and therapy of cardiovascular, inflammatory, immunological, psychological and neurological disorders. They are safe pharmacological agents within the wide range of dose, what was shown in several studies including pregnancy, newborns and elderly and confirmed by the European Food Safety Authority (EFSA) in 2012 [30].

The beneficial effects of omega-3 fatty acids are possibly secondary to their anti-inflammatory, antithrombotic, antiarrhythmic, hypolipidemic and vasodilatory properties [16-19,31-38]. There is an evidence they could improve lipid prolife by lowering triglycerides, decrease insulin resistance and cytokine synthesis [19,34-38]. These effects may be linked with the pathogenesis of NAFLD. Already a number of studies showed efficacy of omega-3 fatty acids in the metabolic syndrome-related conditions [37-41]. Therefore omega-3 fatty acids may be potentially promising medication in the treatment of NAFLD.

To our best knowledge, our study is one of the very few double-blind, placebo-controlled randomized trials testing efficacy of omega-3 in children with NAFLD. Previously Nobili et al. supplemented a group of 60 children with either DHA or placebo for 6 months. The therapy decreased liver steatosis on ultrasound, improved triglycerides and insulin resistance markers, however no change in ALT activity was observed [21]. Further pediatric trials supporting or refuting use of omega-3 fatty in NAFLD are needed.

The review of the literature of randomized trials suggests that wide-range doses (0,8-13,7g per day) of omega-3 fatty acids are safe and may be efficient in NAFLD, however the optimal dose and proportion in the treatment of NAFLD has not been agreed yet [20]. Moreover the evidence is limited in children. We used omega-3 formula containing EPA and DHA, that should combine positive metabolic (mostly EPA) and anti-inflammatory effects (DHA). The composition of the studied supplement consisted of pre-defined DHA/EPA ratio (3:2). The chosen dose and content of omega-3 in our study was decided on the basis of review of the promising results from available open-label studies and it is a compromise that should provide safety and efficacy of therapy [42]. However, the study is testing only one dose of omega-3 instead of multiple doses to determine the dose–response relationship. Use of sunflower oil as a placebo/comparator may be justified because omega-6 are commonly present in a regular diet and the given dose does not influence their nutritional balance.

Weight-dependent dosing may be controversial, but it has to be regarded that the participants are children aged from 6 years to 19 years. The body mass might vary largely in this cohort, therefore differentiation between pediatric and adult doses can be explained. We subjectively set the weight margin at 40 kg and 60 kg for dosage of omega-3 but there are also several studies in children supplementing omega-3 for various indications in weight-dependent manner (per range and per kg) [43,44].

6-month duration of treatment is frequently applied in clinical trials with dietetic supplements like fish oil and it is considered sufficient to achieve therapeutic results and maintain satisfactory compliance [9,13,20].

The strength of our study is a well designed randomization and data collection system, clearly defined dietary counseling and a wide-range of parameters tested. In most previous trials investigating pharmacological treatment for NAFLD, dietetic surveillance was poorly described.

Several methods for assessment of body composition were used in our study (e.g. anthropometry, bioelectric impedance, MRI and DEXA). Among them DEXA becomes the gold standard method giving accurate and noninvasive measure of bone, fat distribution, and muscle tissues during single procedure of total body scan. Data obtained from all these techniques will be studied to estimate the efficacy of treatment and compared between each other to select the most reliable method reflecting changes of body composition in our patients.

The limitation of our study is the definition of NAFLD which is based on ultrasound and ALT (both criteria fulfilled together). Still, this allows to enroll those who present with significant steatosis (as indicated by ultrasound) and possibly inflammation (as indicated by ALT). Liver biopsy is rarely used to select children with NAFLD and for assessment of therapy as there are limited indications for liver biopsy in children.

To minimize possible bias we designed randomized, double-blind trial. Study treatment and placebo have identical appearance of capsules and packaging in plastic pill boxes to ensure the double blind study design. Data of the patients are entered and organized in the electronic case report form (e-CRF). The treatment allocation to the patients is done using a centralized randomization. Randomization is fixed, balanced and stratified according to centre. Both e-CRF and randomization are carried by the external company. Ultrasound was performed each time by the same radiologist, histology of the liver was assessed by two independent pathologists. Advanced lab tests are sent and examined in the central laboratory.

As there is no efficient pharmacological treatment for NAFLD, the positive result of this randomized trial will place omega-3 fatty acids as a useful agent in the treatment of NAFLD in children which can be safely applied together with lifestyle modification. No or negative effect of supplementation will add valuable evidence against its use in NAFLD. Nevertheless, final findings are expected to strongly contribute to the knowledge base and public health guidelines regarding use of omega-3 fatty acids in NAFLD, metabolic syndrome and obesity-related diseases.

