Recently Parker et al. published systematic review and meta-analysis of studies of omega-3 LC-PUFA (long-chain polyunsaturated fatty acids) supplementation in adults with NAFLD [20]. Nine studies (5 RCTs), involving 355 individuals were included. Patients were given either omega-3 LC-PUFA or control treatment. Duration of therapy ranged from 8 weeks to 12 months, as well as the dose of LC-PUFA - from 0,25g to 13,7g per day. In conclusion of the review, omega-3 fatty acids were claimed beneficial vs. placebo in reducing liver fat (estimated by liver biopsy, ultrasound or 1H-MRS) (effect size = ˙0.97, 95% CI: ˙0.58 to ˙1.35, p <0.001) and decreasing AST (effect size = ˙0.97, 95% CI: ˙0.13 to ˙1.82, p = 0.02) but not ALT activity. However the current data are not sufficient to set the optimal dose of LC-PUFA in NAFLD.

So far there has been only one randomized controlled trial that assessed efficacy of LC-PUFA in children with NAFLD [21]. Patients were assigned to receive 250 mg or 500 mg of DHA (docosahexaenoic acid) per day or placebo for 6 months. Beneficial results of DHA were expressed in the improvement of level triglycerides, markers of insulin resistance and liver fat assessed by ultrasound. DHA did not show significant effect on ALT activity.

Below we describe design of our multicenter, randomized, double-blind, placebo-controlled trial of omega-3 LC-PUFA supplementation in children with NAFLD.

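### The Discussion would count a null result as evidence against omega-3, but a non-significant test at 38 per arm leaves moderate benefits open, and sometimes the planned 30 points, unless read from the confidence interval

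*Protocol article*

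**What the plan says.** The Sample size section of the protocol article plans for a "difference in the treatment effect of 30% (45% in experimental group vs. 15% in control group". The significance level is set at 0.05 and the power at 80%. The section gives a total of 80 and adds: "The number of 80 children accounted for approximately 20% withdrawals or losses". The Results section reports 76 children randomised, 38 to each arm.

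The Statistical analysis section tests the primary endpoint with a chi-square or Fisher exact test of no difference, and states: "The differences will be regarded significant at p<0.05". The article gives no smallest worthwhile difference and no equivalence margin.

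The closing paragraph of the Discussion then says: "No or negative effect of supplementation will add valuable evidence against its use in NAFLD".

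On prior evidence, the Background reports that the adult meta-analysis found no benefit on ALT. Of the one earlier paediatric randomised trial it says: "DHA did not show significant effect on ALT activity".

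**The concern.** The trial is sized to detect a tripling of the response rate. A superiority test that fails to reject can mean that the treatment does nothing. It can also mean that the treatment has a moderate effect which a trial of this size usually misses. Only the estimate and its interval tell these apart, and the Discussion sentence refers to neither.

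A null result is a realistic prospect, because the article's own background reports no ALT effect in either earlier source. The article also expects its findings to inform public health guidelines. If a non-significant result with a wide interval were reported as evidence against use, readers could discard a benefit that the data had left open.

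**Working it through.** **Inputs.** Response rates 45% and 15%, α = 0.05, power 80%, about 20% losses, total 80 (Sample size). Chi-square or Fisher exact test at p<0.05 (Statistical analysis). 38 per arm (Results). Assumptions: a two-sided test, since sidedness is not stated; benefits of 10 to 20 points as the range of interest, since no smallest worthwhile effect is given; and, for one sensitivity figure only, 30 evaluable per arm (38 × 0.8 = 30.4).

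**Step 1: the plan's own figure.** With unpooled variance,

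n per arm = (1.96 + 0.842)² × (0.45 × 0.55 + 0.15 × 0.85) / 0.30² = 7.849 × 0.375 / 0.09 = 32.7, so 33.

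33 × 1.2 = 39.6, so 40 per arm and 80 in total. The stated number reproduces. Dividing by 0.8 instead gives 32.7 / 0.8 = 40.9, so 41 per arm and 82 in total, which is close.

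**Step 2: power for smaller benefits.** For each true difference, sum the binomial probabilities of all pairs of responder counts that give p<0.05, with 15% response in control. The chi-square test is taken without continuity correction.

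| True difference | 38 per arm, Fisher | 38 per arm, chi-square | 30 per arm (assumed), Fisher | 30 per arm (assumed), chi-square |
|---|---|---|---|---|
| 30 points | 78% | 84% | 64% | 74% |
| 20 points | 44% | 53% | 33% | 44% |
| 15 points | 26% | 35% | 19% | 28% |

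At 38 per arm, a true doubling from 15% to 30% would be missed in 65% to 74% of trials.

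**Step 3: what particular null results would exclude.** Newcombe's interval for a difference d = p₁ − p₂, with Wilson limits (l, u) for each arm, is

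lower = d − √[(p₁ − l₁)² + (u₂ − p₂)²], upper = d + √[(u₁ − p₁)² + (p₂ − l₂)²].

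For 12/38 against 6/38:
- p₁ = 0.316, Wilson limits 0.191 to 0.475
- p₂ = 0.158, Wilson limits 0.074 to 0.304
- d = 0.158
- lower = 0.158 − √(0.125² + 0.146²) = 0.158 − 0.192 = −0.034
- upper = 0.158 + √(0.159² + 0.084²) = 0.158 + 0.179 = 0.337

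The same method for other counts, with 6/38 (about the planned 15%) in control:

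| Omega-3 | Control | Difference | 95% CI (points) | Chi-square p | Fisher p | 30 points excluded? |
|---|---|---|---|---|---|---|
| 6/38 | 6/38 | 0 | −17 to +17 | 1.00 | 1.00 | yes |
| 10/38 | 6/38 | +11 | −8 to +28 | 0.26 | 0.40 | yes |
| 11/38 | 6/38 | +13 | −6 to +31 | 0.17 | 0.27 | no |
| 12/38 | 6/38 | +16 | −3 to +34 | 0.11 | 0.18 | no |
| 13/38 | 6/38 | +18 | −1 to +36 | 0.06 | 0.11 | no |

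All five are non-significant by either test. The first two are evidence against the planned effect and the last three are not. None excludes a 10- or 15-point benefit.

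**The case against.** **The sentence says that a null result will add evidence, not that it settles the matter.** This is fair. The article states no rule that p≥0.05 proves lack of benefit, and a reader who infers one goes beyond the text. Elsewhere the Discussion calls for further paediatric trials that may support or refute use. Still, the sentence sets no condition on the estimate, and for a result such as 12/38 against 6/38 it would be unsound.

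**A null result near zero is informative.** This also stands. With 6/38 in control, up to 10/38 on omega-3 excludes the 30 points that the trial was designed to find.

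**Nothing worthwhile is defined.** Correct, so the range of 10 to 20 points is an assumption. The planned 30 points is the only benchmark in the document.

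**A reader might infer that the trial is badly underpowered for its own target.** The documents do not support this. At 38 per arm, exact power for 45% against 15% is 78-84%, close to the planned 80%. It falls to 64-74% only if 20% of the 76 are lost, and the article reports no such loss.

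**A reader might also infer that the trial claims to prove safety,** because the Discussion says that a positive result would establish omega-3 as an agent "which can be safely applied together with lifestyle modification". The documents do not support that either. The abstract, the Background and the Discussion take safety as given from outside studies and a regulator's opinion. The closing paragraph repeats that premise and does not present safety as something 38 treated children will show. No point is made on safety here.

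**Reporting a confidence interval is a detail an article may leave to the analysis plan.** Its absence alone would be no finding. The point concerns an interpretation that the article does state.

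**Conclusion.** The point holds as one of interpretation. The advance reading of a null result is too broad for a superiority test with 38 per arm. Power is 44-53% for a 20-point benefit and 26-35% for 15 points. Some non-significant results (11 to 13 responders of 38 against 6 of 38) leave even the planned 30-point effect inside the interval, while flatter ones exclude it but leave 10 to 15 points open. These figures assume a two-sided test, a control response near the planned 15% and no losses from the 76. The sample size stands, and no change to conduct is called for.

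**What to change.** For the primary endpoint, report the responder risk difference with its 95% confidence interval (Newcombe's, for example) beside the p-value. Reword the Discussion sentence along these lines: a non-significant result will be taken as evidence only against benefits larger than the upper confidence limit, with the planned 30-point difference as reference, and as inconclusive for benefits within the interval.

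The article says that the full analysis is still to come, so the change can be made before results are read. The cost is one interval and one sentence. The downside is a weaker claim after a null result.
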